### Outcome measures

The outcome measures that will be assessed in the STEERING trial are summarized in Table 1. The primary outcome is the difference on the Movement Disorders Society Unified Parkinson’s Disease Rating Scale – Motor Evaluation (MDS-UPDRS-ME) [13] score in off-medication state with stimulation turned on between ring-mode DBS and directional DBS setting.

**Table 1 Tab1:** Outcome measures

**Outcome measure**	**Domain**	**Best score**	**Worst score**
MDS-UPDRS-ME	Motor symptoms	0	132
MDS-UPDRS-ADL	Motor aspects in Activities of daily living	0	52
MDS-UPDRS-MC-A	Dyskinesias	0	8
PDQ-39	Quality of life	0	100
LED	Medication use	N/A	N/A
Stimulation settings	Stimulation	N/A	N/A
Likert scale about quality of walking	Motor symptoms	1	5
Likert scale about speech	Motor symptoms and adverse-effects	1	5
Adverse-effects	Adverse-effects	N/A	N/A
Therapy choice at end of trial	N/A	N/A	N/A

*Led* levodopa equivalent dose, *MDS-UPDRS-ADL* Movement Disorders Society Unified Parkinson’s Disease Rating Scale Activities of Daily Living, *MDS-UPDRS-MC-A* Movement Disorders Society Unified Parkinson’s Disease Rating Scale Motor Complications–Dyskinesia, *MDS-UPDRS-ME* Movement Disorders Society Unified Parkinson’s Disease Rating Scale – Motor Evaluation, *N/A* Not applicable, *PDQ-39* Parkinson’s Disease Questionnaire 39

Secondary outcome measures consist of MDS-UPDRS-ME in on-medication state with stimulation turned on, MDS-UPDRS Activities of Daily Living (MDS-UPDRS-ADL) [13], MDS-UPDRS Motor Complications–Dyskinesia (MDS-UPDRS-MC-A) [13], disease related quality of life measured with the Parkinson’s Disease Questionnaire 39 (PDQ39) [14], stimulation-induced adverse-effects, antiparkinsonian medication use expressed in Levodopa Equivalent Dose (LED) [15], two 5-point Likert scales concerning quality of walking and of speech and DBS-parameters. As stated before, patients’ therapy preference is measured at the end of the study.

### Statistics

The sample size calculation was carried out separately for the responder group and the non-responder group. The minimum clinically important differences between ring-mode and directional DBS for the responder and non-responder groups, respectively, were three points and five points on the MDS-UPDRS-ME [16, 17]. For the responder group, we calculated a required sample size of 58 patients (29 patients in each sequence group) to detect an intra-individual difference of three points on the MDS-UPDRS-ME in off-medication state with an assumed intra-individual standard deviation (SD) of 10, 80% power and at 5% significance level. For the non-responder group, we calculated a required sample size of 34 patients (17 patients in each sequence group) to detect an intra-individual difference of five points on the MDS-UPDRS-ME in the off-medication state with an assumed intra-individual standard deviation (SD) of 10, 80% power and at 5% significance level. Considering a drop-out rate of 10% in each group, 64 responders and 38 non-responders will be included. The total sample size will be 102 patients.

Statistical analysis will be based on the intention-to-treat principle. In all analyses, statistical uncertainties will be expressed in 95% confidence intervals (CI). The primary outcome is the difference between ring-mode and directional DBS settings on the off-medication state MDS-UPDRS-ME. This analysis will be performed for responder and non-responder groups separately and for the total study population (*i.e.*, responders and non-responders pooled). Paired t-tests will be used to assess these differences, or, if not normally distributed, a Wilcoxon signed-rank test. Differences will be considered significant at *p* < 0.05 without correcting for multiple comparisons.

It is unlikely that the cross-over will have a sequence effect since the primary outcome is an objective outcome measure and will not be influenced by the patient's perspective. However, the possibility of a sequence effect cannot be ruled out. A possible sequence effect will be evaluated descriptively, as a statistical analysis cannot verify this effect [18].

We will use mixed model analysis and per-protocol analyses to evaluate the robustness of the results and to address the issue of missing data. Patients will be excluded from the per-protocol analyses if they receive the incorrect form of stimulation after randomisation (*e.g.*, patients who change the by randomisation allocated stimulation parameters) or if they do not have the outcome assessments at the pre-specified time window (56 days, with an accepted range of 28 to 66) from randomisation and cross-over visit, respectively.

Other secondary outcomes consisting of on-medication state administered MDS-UPDRS-ME, MDS-UPDRS-ADL, MDS-UPDRS-MC-A, PDQ39, and LED will be presented as point estimates with unadjusted 95% confidence intervals without *p*-values. Patient preference, two 5-point Likert scales concerning quality of walking and of speech, and stimulation-induced adverse-effects will be compared between the ring-mode and directional DBS settings with appropriate non-parametric statistics.

Baseline values and the stimulation parameters of the ring-mode and directional-mode will consist of both categorical (*e.g.*, sex, occurrence of stimulation induced adverse-effects) and continuous variables (*e.g.*, age, disease duration, LED). These data will be presented quantitatively in tables.

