**Methods:**

The STEERING study is a prospective multi-centre double-blind randomised crossover trial. Inclusion criteria are Parkinson’s disease, subthalamic nucleus DBS in a ‘classic’ ring-mode setting for a minimum of six months, and optimal ring-mode settings have been established. Participants are categorised into one of two subgroups according to their clinical response to the ring-mode settings as ‘responders’ (*i.e.*, patient with a satisfactory effect of ring-mode DBS) or ‘non-responder’ (*i.e.*, patient with a non-satisfactory effect of ring-mode DBS). A total of 64 responders and 38 non-responders will be included (total 102 patients). After an optimisation period in which an optimal directional setting is found, participants are randomised to first receive ring-mode DBS for 56 days (range 28–66) followed by directional DBS for 56 days (28–66) or vice-versa. The primary outcome is the difference between ring-mode DBS and directional DBS settings on the Movement Disorders Society Unified Parkinson’s Disease Rating Scale – Motor Evaluation (MDS-UPDRS-ME) in the off-medication state. Secondary outcome measures consist of MDS-UPDRS-ME in the on-medication state, MDS-UPDRS Activities of Daily Living, MDS-UPDRS Motor Complications–Dyskinesia, disease related quality of life measured with the Parkinson’s Disease Questionnaire 39, stimulation-induced side-effects, antiparkinsonian medication use, and DBS-parameters. Participants’ therapy preference is measured at the end of the study. Outcomes will be analysed for both responder and non-responder groups, as well as for both groups pooled together.

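### The responder sample size of 58 does not follow from its stated inputs: 3 points, SD 10, 80% power and a 5% level need 90 patients, and 58 gives about 61% power

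*Protocol article*

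**What the plan says.** The Statistics section of the protocol article sizes the two strata separately.

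- Responders: "we calculated a required sample size of 58 patients (29 patients in each sequence group) to detect an intra-individual difference of three points" on the off-medication MDS-UPDRS-ME.
- Non-responders: "we calculated a required sample size of 34 patients (17 patients in each sequence group) to detect an intra-individual difference of five points" on the same scale.

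Both calculations carry the same assumptions: "with an assumed intra-individual standard deviation (SD) of 10, 80% power and at 5% significance level". The planned analysis is the same for both: "Paired t-tests will be used to assess these differences, or, if not normally distributed, a Wilcoxon signed-rank test". After a 10% drop-out allowance, the Abstract gives the recruitment target as "A total of 64 responders and 38 non-responders will be included (total 102 patients").

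The section treats 3 and 5 points as the minimum clinically important differences for responders and non-responders respectively. It makes the responder comparison one of three analyses of the primary outcome, beside the non-responder and pooled comparisons.

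**The concern.** The two calculations differ in one input only, the target difference. With SD, power and level fixed, the required number rises roughly with the inverse square of that difference. Going from 5 points to 3 should therefore multiply the sample size by about 25/9 = 2.8. The stated numbers rise by only 58/34 = 1.7. No single method or reading of the SD can produce both.

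The responder stratum has its own stated minimum important difference and its own sample size, so readers will judge its result against the claimed 80% power. The Discussion says that ring-mode programming can continue if no benefit of directional stimulation is shown. If the SD really is 10, a true 3-point benefit in responders would be missed about 39% of the time, not 20%. A null responder result would then be read as stronger evidence than it is.

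**Working it through.** **Inputs** (all from the Statistics section)

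| | Responders | Non-responders |
|---|---|---|
| Difference δ | 3 points | 5 points |
| SD | 10 | 10 |
| Power, level | 80%, 5% | 80%, 5% |
| Test | paired t | paired t |
| Stated n | 58 | 34 |

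The sample-size text does not say whether the level is one- or two-sided. Two-sided is assumed, in line with the 95% confidence intervals planned for all analyses. The one-sided case is checked in step 4.

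**Method.** For n pairs, the noncentrality is λ = (δ/SD)·√n. Power is the probability that a noncentral t with n − 1 degrees of freedom and noncentrality λ exceeds the two-sided 5% critical value in absolute size. The required n is the smallest that reaches 80%. Using n − 2 degrees of freedom, as for a two-sequence crossover, gives the same required numbers.

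**Step 1: reproduce the plan's non-responder figure.** δ = 5, SD of the paired difference = 10.
- n = 33: λ = 0.5·√33 = 2.872, power 79.5%.
- n = 34: λ = 0.5·√34 = 2.915, power 80.8%.

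The required n is 34, an exact match. This identifies the method: two-sided, with 10 as the SD of the within-patient difference.

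**Step 2: the same method for responders.** δ = 3, SD = 10.
- Normal approximation: 7.849 × 10² / 3² = 87.2, so 88.
- n = 89: λ = 0.3·√89 = 2.830, power 79.9%.
- n = 90: λ = 0.3·√90 = 2.846, power 80.4%.

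The required n is 90 (45 per sequence), or 90/0.9 = 100 with 10% drop-out. The plan has 58 and 64.

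**Step 3: what the stated numbers deliver at SD 10.**
- n = 58: λ = 0.3·√58 = 2.285, critical value 2.002, power 61.3%. The chance of missing a true 3-point difference is 38.7%.
- All 64 enrolled with no drop-out: λ = 0.3·√64 = 2.40, power 65.7%.
- Difference detectable with 80% power at n = 58: about 3.74 points.

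**Step 4: can another reading give 58?**

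| Reading | Responders (stated 58) | Non-responders (stated 34) |
|---|---|---|
| Two-sided, difference SD 10 | 90 | 34 |
| One-sided 5%, difference SD 10 | 71 | 27 |
| 10 is the SD of one measurement (difference SD 10·√2 = 14.14) | 177 | 65 |
| Difference SD 10/√2 = 7.07 | 46 | 18 |
| Difference SD 8 | 58 | 23 |

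No row gives both stated numbers. Holding 3 points, 80% power and two-sided 5%, the figure of 58 comes from SD 8 (λ = 0.375·√58 = 2.856, power 80.2%). Holding SD 10 instead, it comes from a difference of about 3.75 points, which has the same λ and power.

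**The case against.** The strongest reply is that this may be only a reporting slip. If the responder calculation used SD 8, then 58 is right, the power is about 80% as claimed, and nothing is wrong with the trial's size. That stands as a possibility: the 61% power and the 39% miss rate hold under the printed SD of 10, and the document does not show which input is wrong. SD 8 is an inference from an exact match, and about 3.75 points at SD 10 fits equally well, although the stated 3-point minimum difference makes the SD the likelier slip.

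It is also fair to say that low power bears on a null result and does not undermine a significant one, and that the promised confidence intervals would show the imprecision of a null result. This limits the harm but does not make the statement correct.

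Three side issues carry little weight. The term intra-individual SD can be read in two ways, but the match at 34 settles it as the SD of the difference. Recruiting 64 rather than 65 is a matter of convention (58 × 1.10 = 63.8; 58/0.9 = 64.4). Power for the pooled analysis is useful context, not part of the error.

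That the article condenses a fuller protocol is no answer, because every input is printed and the printed inputs contradict each other.

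**Conclusion.** The concern holds. The responder sample size, difference, SD, power and level given in the Statistics section cannot all be true. With the printed SD of 10, a 3-point difference needs 90 completers, and the planned 58 give 61% power instead of 80%, with about 3.7 points detectable at 80%. This assumes a two-sided paired t-test with 10 as the SD of the directional-minus-ring difference, the reading under which the plan's own 34 non-responders reproduce exactly. If the responder calculation in fact used SD 8, then 58 stands and the printed SD is wrong. The text needs correcting in either case. It must be fixed, because it misstates the sample size or power of a primary-outcome analysis.

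**What to change.** The sponsor should establish which input the responder calculation used and correct the Statistics section accordingly. No further enrolment is needed.

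- **If SD 10 is right:** keep 58 completers (64 recruited), and state that this gives 61% power for 3 points and 80% power for about 3.7 points.
- **If SD 8 was used:** state SD 8 for responders, justify why it is smaller than the 10 assumed for non-responders, and show power for 3 points with 58 completers over SD 8 to 10: 80% at 8, 70% at 9 and 61% at 10.

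In both cases, define the SD as that of the within-patient directional-minus-ring difference and say that the test is two-sided. Optionally, add that the pooled 58 + 34 = 92 completers have 81% power for 3 points at SD 10, and state the drop-out rounding convention.

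The cost is wording only. If SD 10 is kept, the stated power for responders becomes less favourable.

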At the randomization visit, the researcher records their prediction of whether or not the directional program will lead to a greater improvement of Parkinsonian symptoms when compared to the ring-mode. Patients are randomised into a crossover study design using ALEA randomisation software (www.aleaclinical.eu). Allocation is set to a 1:1 ratio with block sizes of two and four. Patients are stratified by their responder/non-responder status. Each participating patient receives both directional and ring-mode DBS treatment for a period of two months (56 days, with an accepted range of 28 to 66). Patients are randomised to receive directional stimulation as the first intervention and ring-mode stimulation as the second (directional-first group) or to receive the two interventions in reversed order (ring-mode-first group). The physician co-investigators and nurse specialists performing the programming are not blinded to patient allocation. Participants and trial nurses doing the assessments are blinded to the DBS settings (*i.e.*, ring-mode or directional DBS). The statistician analysing the results of the trial will be blinded as well.

At the end of the first intervention visit (*i.e.*, before cross-over) and at the end of the second intervention visit (*i.e.*, at the end of follow-up) the primary and secondary outcome measurements and questionnaires are performed. At the end of the second intervention, whilst still in blinded condition, the patient chooses which of the two programs they want to keep: the first or second intervention. After the participant finished all assessments, they may be unblinded and return to regular DBS follow-up.

Approval of the medical ethical committee of both participating centres was obtained. The STEERING-study conforms to the principles of the Declaration of Helsinki (version 2008). Study monitoring and data management are performed in accordance with the International Conference on Harmonisation—Good Clinical Practice guidelines. It is an investigator-initiated study. Funding organizations did not have an influence on the design, execution, data analysis, or participation in article drafting.

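### The pooled primary paired t-test has no responder term although the stratum sizes are fixed by design, so its standard error is on average slightly too wide if the strata respond differently; a stratified error term costs nothing

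*Protocol article*

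**What the plan says.** In the protocol article, under Study procedures and randomisation, the order of the two treatments is randomised within responder status: "Patients are stratified by their responder/non-responder status". Under Statistics, the size of each stratum comes from its own calculation: 58 responders and 34 non-responders, raised to 64 and 38 for drop-out. The minimum important differences used there "were three points and five points on the MDS-UPDRS-ME", for responders and non-responders respectively, with an SD of 10 in both.

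The primary comparison is then made three times: "This analysis will be performed for responder and non-responder groups separately and for the total study population". The method is the same each time: "Paired t-tests will be used to assess these differences, or, if not normally distributed, a Wilcoxon signed-rank test". No responder term is given for the pooled comparison. A mixed model is planned as a robustness analysis, and its terms are not listed.

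The Discussion allows that benefit may occur in one group only, or in both to different degrees. It says that a significant pooled difference in favour of directional stimulation could make it the treatment standard, and it cites greater power as an advantage of pooling.

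**The concern.** A paired t-test on all patients estimates the variance of the within-patient differences around a single overall mean. If responders and non-responders benefit to different degrees, the distance between the two stratum means is counted in that variance. The numbers in each stratum are quotas, so the distance does not make the pooled mean vary from one repetition of the trial to the next. It therefore does not belong in the standard error of the mean effect at those shares.

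At stake is some precision and power in the comparison that the Discussion ties to a change of standard treatment. The loss arises only when the strata respond differently. The test is named in the text, so this concerns a stated method and not a detail left open.

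**Working it through.** **Inputs.** From Statistics: nR = 58, nN = 34, n = 92 (the numbers before drop-out inflation); SD 10; effects 3 and 5. From the Discussion: benefit in one stratum only is possible, represented here by 0 and 5. The pair 0 and 8 is my illustration and is not in the article. I take the SD of 10 as that of the within-patient difference, equal in both strata.

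**The plan's own figures.** The article gives no sample size or power for the pooled test, so there is none to reproduce. For the strata, a two-sided paired t-test at 5 points, SD 10 and 80% power needs 34 patients, which matches and supports my reading of the SD. At 3 points it needs 90, not 58, and 58 patients give about 61% power. That mismatch is a separate and much larger matter. I use 58 here only as the stated stratum size.

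**Formula.** The expected variance used by the unstratified test is

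σ² + [nR·nN / (n(n − 1))] × gap², with 58 × 34 / (92 × 91) = 1972 / 8372 = 0.2355.

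The stratified variance is σ² = 100, giving SE = 10 / √92 = 1.0426.

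| Effects (responder, non-responder) | Gap | Unstratified variance | SE, unstratified | SE, stratified | Excess |
|---|---|---|---|---|---|
| 3, 5 | 2 | 100 + 0.94 = 100.94 | 1.0475 | 1.0426 | 0.5% |
| 0, 5 | 5 | 100 + 5.89 = 105.89 | 1.0728 | 1.0426 | 2.9% |
| 0, 8 | 8 | 100 + 15.08 = 115.08 | 1.1184 | 1.0426 | 7.3% |

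At 3 and 5 points the 95% CI half-width is 2.081 against 2.071, a difference of 0.01 point. With 64 + 38 analysed, the excess at 3 and 5 is the same (0.9948 against 0.9901).

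**Simulation** (40,000 trials, 58 + 34, SD 10), power unstratified against stratified:
- equal effects: 81.2% for both;
- 3 and 5: 94.4% against 94.5%;
- 0 and 5: 39.4% against 41.5%, with CI coverage 95.7% against 95.0%;
- 0 and 8: 75.9% against 80.1%.

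**How regular the excess is.** Within one trial the unstratified SE is the larger when (nR·nN/n) × (observed gap)² exceeds the within-stratum variance. Here that means an observed gap above 10 / √21.43 = 2.16 points. It happens in about 50% of trials at a true gap of 2, about 91% at 5 and over 99% at 8.

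**Mixed model.** In a simulation with effects 0 and 8 and a random patient intercept, the treatment SE was 1.107 without responder status and 1.107 with it as a main effect. It fell to 1.031 only with a treatment-by-responder term.

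**The case against.** The strongest case against is that a plain paired t-test is valid and that nothing would change at the article's own figures: 0.5% in the SE and 0.01 point in the half-width. That stands, and it fixes the weight of this point.

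A second objection concerns the target. The Background asks about the whole DBS population, and the Discussion calls the pooled set representative. If the stratum mix were a random draw, the gap would be genuine sampling variation. The SE would be √[(100 + (58/92)(34/92) × 4) / 92] = 1.047 at 3 and 5, which is what the unstratified test gives. But the 64:38 split follows from two power calculations and is not a random draw, so the objection does not fit the stated design.

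Third, patients are their own controls and stratification governs only the order of treatment. Differences in score level between strata cancel. A reader might infer that stratified randomisation by itself makes the unstratified SE wrong. It does not: the excess needs fixed stratum sizes together with unequal treatment effects.

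Two other stronger readings are tempting. One is that the interval is too wide whenever the effects differ. The excess is an average, and at a 2-point gap it appears in only about half of trials. The other is that the plan assumes unequal effects. Three and five points are minimum important differences for sample size, and the Discussion calls unequal effects only possible.

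Fourth, where only non-responders benefit, extra pooled power could favour a general change of standard on one group's benefit. That is a fair caution about interpreting the pooled result. The separate stratum analyses, already planned, will show it. It is not a reason to keep a wider error term.

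**Conclusion.** The point holds as a low-cost improvement. With stratum sizes fixed and unequal treatment effects, the pooled SE is on average too wide: negligibly at 3 and 5 points (0.5%), modestly at 0 and 5 (2.9%), and by 7.3% in the illustrative case of 0 and 8. These figures assume an SD of 10 for the paired difference in both strata, 58 + 34 analysed patients, and a pooled effect defined at those shares. A larger SD shrinks the excess: at 14.14 it is 0.24% for 3 and 5.

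A reader might infer that the pooled result is invalid or its error rate inflated. Neither is so: the error is on the conservative side, and coverage is at or above 95%.

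**What to change.** In Statistics, add for the total population: the within-patient differences are analysed with responder status as a fixed factor. The mean effect is reported weighted by the analysed stratum shares, with SE and 95% CI from the pooled within-stratum variance on n − 2 degrees of freedom.

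The weights should be the analysed shares. The estimate then equals the plain mean difference. With enrolled shares and uneven drop-out it would move. For example, with 64 + 30 analysed and effects 3 and 5, the plain mean is (192 + 150) / 94 = 3.64, while enrolled shares give (192 + 190) / 102 = 3.75.

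In the planned mixed model, the equivalent is a treatment-by-responder term averaged over the same shares; a responder main effect alone does not do it. The signed-rank fallback is not covered by this change.

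The cost is one sentence and one degree of freedom, with no new data or patients. If the effects are equal, power is essentially unchanged.

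### The primary paired t-test or Wilcoxon takes no account of period and uses complete pairs only; the mixed model, with period named as a term, should be primary

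*Protocol article*

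**What the plan says.** All of the following is in the protocol article, Statistics section, unless another section is named.

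- **Primary test**, for responders, non-responders and the pooled set: "Paired t-tests will be used to assess these differences, or, if not normally distributed, a Wilcoxon signed-rank test".
- **Analysis principle:** "Statistical analysis will be based on the intention-to-treat principle".
- **Order effects:** these are discussed only as a sequence effect. "It is unlikely that the cross-over will have a sequence effect since the primary outcome is an objective outcome measure", and then "A possible sequence effect will be evaluated descriptively, as a statistical analysis cannot verify this effect". A period effect is not mentioned.
- **Mixed model:** "We will use mixed model analysis and per-protocol analyses to evaluate the robustness of the results and to address the issue of missing data". Its terms are not listed.
- **Allocation** (Study procedures and randomisation): "Allocation is set to a 1:1 ratio with block sizes of two and four", stratified by responder status.
- **Sample size:** 34 non-responders (17 per sequence) for a 5-point difference and 58 responders (29 per sequence) for a 3-point difference, each with SD 10, "80% power and at 5% significance level". After 10% drop-out these become 38 and 64.

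**The concern.** Three features of the stated primary test are at issue.

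1. **Period.** If scores shift between the first and second assessment for any reason common to both sequences, the shift enters the within-patient differences with opposite signs in the two sequences. A paired test counts that spread as noise. The article's reason for a descriptive check is that a sequence effect cannot be verified statistically. That reason does not extend to period, which is estimable in this design.
2. **Complete pairs.** Both named tests need two scores per patient. At the planned drop-out, 4 of 38 non-responders and 6 of 64 responders would leave the headline analysis. This sits uneasily with the stated intention-to-treat principle. The Discussion also says some patients found it hard to stay on a setting, so loss may be related to treatment.
3. **Test chosen from the data.** Normality would be judged in each of three analyses. One could end on a mean difference and another on a rank-based quantity, although the targets of 3 and 5 points are differences in score. When the differences are skewed, which is when the switch is likely to operate, the two quantities diverge.

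At stake are the width of the primary confidence interval, a small avoidable bias, and whether the three results can be compared.

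**Working it through.** **Inputs.** From the article: n = 34 (17/17), difference 5; n = 58 (29/29), difference 3; SD 10, read as the SD of the within-patient difference; 5% level, taken as two-sided because 95% intervals are planned. Assumed, because the article gives none: a period shift π of 3 or 5 points, a completer split of 19/15, and a within-patient correlation of 0.5 to 0.8.

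**Plan's own figure.** A paired t-test with n = 34, difference 5 and SD 10 has 80.8% power (noncentral t), so 34 reproduces. The responder figure of 58 does not: at 3 points and SD 10 its power is 61%. That is a separate matter and does not affect this point.

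**Model.** Let D = directional minus ring, with true effect τ. Then D has mean τ − π in directional-first patients and τ + π in ring-first patients, and SD 10 in both.

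**Balanced sequences.** The shift cancels from the mean of D, so the paired estimate is unbiased and its true standard error stays at 10/√34 = 1.715. The estimated variance is inflated: its expectation is 100 + π² × n/(n − 1).

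- π = 3: 100 + 9 × 34/33 = 109.3, SD 10.45
- π = 5: 100 + 25 × 34/33 = 125.8, SD 11.21

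Rejection rates follow by treating the mean as normal with its true standard error and the sum of squares divided by 100 as noncentral chi-square, with n − 1 degrees of freedom and noncentrality nπ²/100:

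| n = 34, balanced | π = 0 | π = 3 | π = 5 |
|---|---|---|---|
| Paired t, power at 5 points | 80.8% | 78.2% | 73.5% |
| Paired t, type I error | 5.0% | 4.1% | 2.9% |
| Period-adjusted, power | 80.7% | 80.7% | 80.7% |
| Period-adjusted, type I error | 5.0% | 5.0% | 5.0% |

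Simulation of the same set-up agrees within about one percentage point. For responders (n = 58, 3 points, SD 10), paired power goes from 61% to 58% and 52%, and adjusted power stays at 61%.

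Putting the inflated SD straight into a noncentral t would overstate the loss, because it treats a fixed shift as random variation in the mean.

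**Unequal completers.** The bias of the paired mean is π × (difference in completers)/n:

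- π = 3: 3 × (19 − 15)/34 = 0.35 points
- π = 5: 5 × (19 − 15)/34 = 0.59 points

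The sign depends on the direction of the shift and on which sequence loses more patients. The adjusted estimate averages the two sequence means with equal weight, so it is unbiased. Its standard error is 10 × ½ × √(1/19 + 1/15) = 1.727, against 1.715 when balanced. The paired test's type I error at this split is about 4.5% (π = 3) and 3.8% (π = 5).

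**How likely is 19/15?** From 19/19 randomised, all four drop-outs must fall in one sequence. If drop-out is unrelated to sequence, the probability is 2 × C(19,4)/C(38,4) = 2 × 3,876/73,815 = 10.5%. Drop-out related to tolerability could make it likelier.

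**Single-period patients.** Generalised least squares with a period term, adding 4 one-score patients to 34 pairs, lowers the standard error from 1.715 to 1.690 (correlation 0.5) or 1.705 (correlation 0.8). With 6 added to 58 pairs it goes from 1.313 to 1.296 or 1.306. The gain is about 1% to 3% of variance.

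**The case against.** The strongest reply is that little is lost. Allocation is 1:1 in small blocks within responder strata, so sequences will be nearly equal and the paired estimate nearly unbiased. Enrolment is already inflated for drop-out, a mixed model is already planned for missing data, and intention-to-treat can be read as analysing patients by allocated sequence, in contrast to the per-protocol exclusions. Model terms and the normality criterion may properly sit in an analysis plan. Most of this stands and limits the size of the point. It does not remove it: the article fixes the primary test, and no further detail can give a paired t-test or signed-rank test a period term or make it use a single score.

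Four stronger readings are tempting, and the document does not support them.

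- *The planned mixed model already handles period, so swapping the two analyses is enough.* The article ties that model to robustness and missing data and names no period term. The term has to be added.
- *The paired test inflates false positives.* In the cases computed it is conservative, also at 19/15.
- *Patients reach randomisation on a stable directional program, so ring-first patients change setting and directional-first patients do not, and period adjustment would correct this.* That describes prior exposure differing by sequence, which is carry-over. A fixed period effect does not remove it; with equal sequences the paired and adjusted point estimates are identical. The Discussion treats carry-over separately and expects it to have waned by the four-week minimum.
- *Including single-period patients recovers substantial power.* It recovers about 1% to 3% of variance.

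**Conclusion.** The point holds as a modest improvement that costs almost nothing. The stated primary analysis ignores an estimable period effect, drops patients with one score and picks its test from the data. With balanced sequences, assumed shifts of 3 and 5 points cost the non-responder comparison about 3 and 7 percentage points of power. The bias at a 19/15 split is 7% and 12% of the 5-point target (0.35/5 and 0.59/5). With no period shift and equal sequences, neither loss arises. All of these sizes rest on assumed shifts and splits and on reading SD 10 as the SD of differences. The case for keeping single-period patients is consistency with intention-to-treat and validity under missing at random, not precision.

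**What to change.** - Make the mixed model the primary analysis in each of the three sets. Name its terms: fixed effects for treatment and period, plus responder stratum in the pooled set, and a random patient effect. Include every randomised patient with at least one post-randomisation score.
- Move the paired t-test and the Wilcoxon signed-rank test to sensitivity analyses, and delete the rule that chooses between them by normality.
- State that the descriptive check concerns sequence or carry-over, and that period is adjusted for in the model. Do not present the adjustment as a remedy for carry-over.

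The cost is wording and one degree of freedom: at n = 34 with no period shift, power is 80.7% instead of 80.8%. No change to design, visits or sample size follows from this point.
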